**Conclusions:**

This protocol addresses a critical evidence gap in Latin America by integrating psychometric validation and longitudinal evaluation of facial feminization surgery outcomes among transgender women in Chile. The project is expected to develop the first validated Spanish-language quality-of-life instrument specific to facial feminization surgery, alongside multidimensional evidence of surgical outcomes. The findings will inform clinical decision-making, contribute to inclusive patient-centered care, and support the development of evidence-based policies for transgender health in the region.

**International Registered Report Identifier (IRRID):**

DERR1-10.2196/75065

## Introduction

### Background

Some countries face persistent challenges related to health inequities, influenced by factors such as socioeconomic status and geographical distribution. These disparities affect access to health care services across multiple population groups, including transgender individuals.

Transgender women are defined as individuals who identify with the female gender, independent of any medical or surgical interventions they may have undergone [1]. Facial appearance is a key determinant in gender recognition and social perception [2]. Facial characteristics typically associated with masculinity have been linked to increased exposure to social stigma and discrimination, which may contribute to mental health disparities within this population [2-4]. In Chile, available data indicate that the prevalence of depression among transgender individuals is approximately 10 times higher than in the general population, with suicidal ideation rates reaching 68%, compared with 2.2% in the general population [5,6].

Facial feminization surgery is a gender-affirming surgical intervention aimed at modifying facial structures to align with female anatomical norms [7-9]. Although this surgery has been associated with improved psychological and social outcomes, there is limited research evaluating its impact on quality of life using standardized, validated, and population-specific instruments. To date, no studies in Chile have systematically assessed the outcomes of facial feminization surgery, incorporating objective morphological measurements and validated patient-reported outcome measures.

Instruments commonly used to assess quality of life among transgender individuals were originally designed for the general population and later adapted for use in transgender contexts. However, these tools may not comprehensively capture the specific needs and expectations of transgender women undergoing facial feminization surgery [2,3,7,9-12]. Furthermore, most available instruments have been translated from English without undergoing formal validation for use in Spanish-speaking populations, potentially limiting their applicability in Latin American health care settings. Currently, no validated questionnaire exists in Spanish specifically addressing the quality of life of transgender women undergoing facial feminization surgery in Chile [13,14].

The surgery involves modifications to both hard and soft tissues, which can be assessed using cone beam computed tomography (CBCT) and standardized clinical photography. The international literature identifies the frontal-naso-orbital complex (including the forehead, supraorbital crest, frontomalar prominence, temporal ridges, and frontonasal transition) and the mandibular region (chin, mandibular body, angle of the mandible, ascending ramus, and basilar ridge) as the primary anatomical determinants of facial gender. Secondary regions of importance include the nose, zygomatic region, and thyroid cartilage [1,8,15,16]. However, there is a lack of local data in Chile describing the frequency and extent of surgical modifications to these anatomical regions.

Cephalometric differences between male and female facial structures are influenced by biological sex, ethnic background, and genetic inheritance. Typically, male faces have larger craniofacial dimensions, more acute nasolabial angles, and more obtuse mandibular angles, while female face exhibit more convex profiles, smaller nasal dimensions, and less prominent chins [8,15-19].

### Objectives of the Study

This study aims to develop and validate a culturally and linguistically appropriate quality-of-life questionnaire specifically tailored to the transgender population in Chile. It also seeks to evaluate the impact of facial feminization surgery through the analysis of changes in cephalometric and photometric parameters and their association with perceived femininity, as assessed both by third-party evaluators and the participants themselves.

This study hypothesizes that transgender women undergoing facial feminization surgery will experience measurable improvements in quality of life, particularly when facial parameters align more closely with female anatomical standards. In addition, variables such as social participation, employment status, self-perception, and psychosocial stress will be examined to provide a comprehensive understanding of the effects of facial feminization surgery. By integrating multidimensional assessments of psychological well-being, facial morphology, and gender perception, the study aims to generate evidence to inform clinical decision-making and support the development of inclusive, evidence-based health care policies for transgender individuals.

## Methods

### Study Design

This study consists of 2 complementary methodological components: questionnaire development and validation and a longitudinal cohort study.

### Questionnaire Development and Validation

A cross-sectional study will be conducted to develop and psychometrically validate a novel quality-of-life instrument tailored for transgender women undergoing facial feminization surgery in a public hospital in Santiago, Chile. The study will follow the COSMIN (Consensus-Based Standards for the Selection of Health Measurement Instruments) guidelines for the development and evaluation of patient-reported outcome measures (Multimedia Appendix 1). The validation process will include assessments of content validity, structural validity, internal consistency, and reliability in accordance with the COSMIN methodology.

### Longitudinal Cohort Study

A prospective longitudinal cohort analytical study following the STROBE (Strengthening the Reporting of Observational Studies in Epidemiology) guidelines [20] will be conducted to evaluate the effects of facial feminization surgery across three primary domains: (1) quality of life, (2) perception and self-perception of facial femininity, and (3) cephalometric and photometric changes in hard and soft facial tissues (Multimedia Appendix 2).

Quality of life will be assessed using the validated questionnaire, administered preoperatively and at least 12 months postoperatively. Femininity perception will be evaluated through standardized facial photographs assessed by independent raters. Cephalometric and photometric changes will be measured using CBCT and analyzed with Dolphin Imaging software (version 12; Dolphin Imaging and Management Solutions).

### Study Phases

#### Phase 1: Questionnaire Development and Validation

##### Overview

The instrument, titled Quality of Life and Perception of Femininity in Facial Feminization Surgery, will be developed and validated for use in both pre- and postoperative contexts. The development and validation process will follow 5 sequential stages [21,22]. First, a comprehensive review of the scientific literature will be conducted following PRISMA (Preferred Reporting Items for Systematic Reviews and Meta-Analyses) [23] to analyze instruments and tools used to assess quality of life in adult transgender women undergoing facial feminization surgery. The search will be performed in PubMed, Google Scholar, and SciELO databases for studies published between 2010 and 2024 in English or Spanish, using the terms “Quality of life,” “Quality of life instruments,” “Facial feminization surgery,” “Gender affirming surgery,” and “Facial gender affirming surgery” (Multimedia Appendices 3 and 4). Second, the initial construction of the questionnaire will integrate the specific needs and expectations of transgender women undergoing facial feminization surgery, the clinical and technical priorities of the surgical team experienced in facial feminization surgery, and evidence from validated quality-of-life instruments and clinical cases reported by other surgical teams. Third, content validation will be carried out by an expert panel composed of maxillofacial surgeons with experience in facial feminization surgery, sociologists specialized in gender studies, psychologists, public health professionals with expertise in instrument development, and transgender women from civil organizations. Panel members will independently assess the relevance, clarity, language, and cultural appropriateness of each item. A series of meetings will be held between the panel members and the research protocol authors. On the basis of this collaborative process, items will be revised, removed, or added to optimize content validity. Fourth, pilot testing of the preliminary version of the questionnaire will be conducted among transgender women enrolled in the gender identity program at San Juan de Dios Hospital. The objective of this phase will be to evaluate the clarity, acceptability, and comprehensibility of the items, as well as the overall structure and administration time of the instrument. Between 5 and 10 participants will complete the questionnaire in a supervised setting, followed by interviews aimed at identifying any difficulties in item interpretation, relevance of the content, and potential sources of confusion or discomfort. Finally, statistical validation of the questionnaire will involve a larger and more diverse sample of transgender women. Participants will be recruited from multiple sources to ensure variability in sociodemographic backgrounds and health care access. The final version of the questionnaire will be self-administered online.

##### Participants

Participants eligible for the questionnaire validation study must meet the following inclusion criteria: self-identifying as a transgender woman, being aged 18 years or older, living in Chile at the time of questionnaire completion, and being proficient in Spanish (speaking, reading, and comprehension).

##### Recruitment and Questionnaire Distribution

Participants for the validation phase will be recruited through multiple channels to ensure a diverse and representative sample of transgender women in Chile. Recruitment strategies will include telephone outreach to individuals currently enrolled in the gender program at San Juan de Dios Hospital; invitations extended to patients receiving private care from professionals affiliated with the gender program; snowball referrals, whereby participants may suggest other eligible transgender women within their social networks; and open call dissemination through social media platforms and digital networks of civil society organizations.

The questionnaire will be distributed digitally through a hyperlink and hosted on the Google Forms platform. This format will allow participants to complete the instrument remotely at their convenience while ensuring data security and accessibility, and may also help reduce response bias.

##### Sample Size for Questionnaire Validation

Sample size determination for questionnaire validation was based on established methodological recommendations for psychometric studies. While some authors suggest including 5 to 10 participants per item of the instrument, others propose a minimum of 200 participants to ensure sufficient statistical power and stability of factor structures, regardless of the number of items. Following these recommendations, the validation phase of this study will include a minimum of 200 Spanish-speaking transgender women [24,25].

This sample size is deemed sufficient to perform exploratory factor analyses and, when applicable, confirmatory analyses, while also enabling the evaluation of internal consistency and strengthening the generalizability and reliability of the final instrument.

##### Data Analysis

Exploratory and confirmatory factor analyses will be conducted using polychoric correlation matrices and maximum likelihood estimation. Internal consistency will be assessed using Cronbach α, with a threshold of ≥0.70 considered acceptable. All analyses will be independently conducted by 2 researchers to ensure methodological rigor and reproducibility [26].

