## Results

This study was funded in October 2023. Phase 1, corresponding to the development and initial psychometric validation of the Quality of Life and Perception of Femininity in Facial Feminization Surgery questionnaire, was conducted between January 2024 and January 2025. A total of 216 transgender women participated in the study, which exceeded the estimated sample size.

The initial questionnaire design was based on a structured literature review conducted according to PRISMA guidelines, which identified existing tools and dimensions used to assess the quality of life of transgender women undergoing facial feminization surgery (Multimedia Appendices 3 and 4). Data analysis is currently in progress, and the corresponding manuscript is expected to be submitted for publication before the end of 2025.

Concurrently, phase 2 of the study—the longitudinal cohort assessing surgical outcomes—is ongoing. Standardized facial photographs and CBCT scans are being collected for presurgical cephalometric and photometric analysis.

The validated presurgical quality-of-life questionnaire will be administered starting in the fourth quarter of 2025 to more than 30 transgender women currently on the waiting list for facial feminization surgery. The surgeries are planned to take place throughout 2026, with the administration of the postsurgical quality-of-life questionnaire starting 12 months after surgery. Data collection is expected to conclude in 2027.

All relevant data underlying the preliminary findings of this study will be made available through the openICPSR repository. Data will be deidentified to protect participant confidentiality in accordance with ethical guidelines. Access to sensitive data that cannot be fully anonymized will be restricted because of ethical considerations. Requests for access to restricted data can be directed to the Scientific Ethics Committee of San Juan de Dios Hospital, Santiago, Chile, and will be considered on a case-by-case basis.

In case of early study termination, an ethically responsible discontinuation plan will be implemented, including notification to the ethics committee and participants, documentation of reasons, appropriate data analysis, and submission of a final report to ensure transparency and scientific value.

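### Phase 1 specifies maximum likelihood on polychoric correlations with no robust correction, which inflates the confirmatory fit chi-square and makes RMSEA and CFI look worse than they should.

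*Protocol article*

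**What the plan says.** The Data Analysis section for Phase 1 fixes both the input and the estimator: "Exploratory and confirmatory factor analyses will be conducted using polychoric correlation matrices and maximum likelihood estimation". It mentions no scaled test statistic, robust standard errors or least-squares alternative, and it sets no fit criterion.

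The section on sample size for questionnaire validation takes its minimum from a rule of thumb. It reports that "some authors suggest including 5 to 10 participants per item of the instrument" and that "others propose a minimum of 200 participants to ensure sufficient statistical power and stability of factor structures, regardless of the number of items", and then commits to the fixed figure: "the validation phase of this study will include a minimum of 200 Spanish-speaking transgender women". It adds that "This sample size is deemed sufficient to perform exploratory factor analyses and, when applicable, confirmatory analyses". The confirmatory analysis is therefore conditional in that section and unconditional in the Data Analysis section.

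The Results section reports the recruitment: "A total of 216 transgender women participated in the study, which exceeded the estimated sample size". It also says that the analysis is still in progress. The article gives neither the number of items nor the number of response categories. It does not say which participants the confirmatory model will be fitted to.

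**The concern.** Polychoric correlations suit ordinal answers as an input. The difficulty is the pairing with uncorrected maximum likelihood. The normal-theory fit function is calibrated to the sampling variance of Pearson correlations from continuous normal data. A polychoric correlation estimates a latent correlation from coarse categories, so its sampling variance is larger. Read as Pearson noise, that extra noise looks like misfit. The chi-square then exceeds its reference distribution although the model is correct, and the indices built on it (RMSEA, CFI) worsen too.

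Structural validity is one of the properties that Phase 1 sets out to assess, and the resulting questionnaire supplies the quality-of-life and self-perceived femininity measures in Phase 2. A sound structure could be reported as fitting badly. The independent analysis by two researchers would not catch this, because both would apply the same specification.

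**Working it through.** **Plan's own figure.** The 200 is a rule of thumb, so there is no formula to reproduce. Against the per-item rule cited beside it, 200/10 = 20 and 200/5 = 40 items; for 216, 216/10 = 21.6 and 216/5 = 43.2 items.

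**Inputs.** From the article: n = 216, polychoric input, maximum likelihood. Assumed: 15 items, three factors with five items each, all loadings 0.7, factor correlations 0.4, and 5 symmetric, 5 skewed or 3 response categories.

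**Method.** Ordinal data were generated from the true model, two-step polychoric correlations were estimated, and the correctly specified model was fitted by maximum likelihood:

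F = ln|Σ| + tr(SΣ⁻¹) − ln|S| − p, with T = (n − 1)F referred to chi-square.

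Degrees of freedom: 15 × 14/2 = 105 correlations, less 15 loadings and 3 factor correlations, leaves 87. The control was continuous data with Pearson correlations. Each setting had 1000 runs.

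| Data | Mean T/df | Rejected at nominal 5% | Mean CFI | Mean RMSEA | Model SE / empirical SD |
|---|---|---|---|---|---|
| Continuous (control) | 1.04 | 7.5% | 0.994 | 0.013 | 1.00 |
| 5 categories, symmetric | 1.43 | 76% | 0.967 | 0.043 | 0.93 |
| 5 categories, skewed | 1.79 | 98% | 0.942 | 0.059 | 0.90 |
| 3 categories | 2.13 | 99.8% | 0.919 | 0.072 | 0.87 |

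**Consistency check.** RMSEA is approximately √[(T/df − 1)/(n − 1)]. For 5 skewed categories, √(0.79/215) = 0.061; for 3 categories, √(1.13/215) = 0.072. Both agree with the simulated means.

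**Estimates and standard errors.** The last column refers to a factor correlation. Its standard error is too small by about 7%, 10% and 13%. Its mean estimate is 0.402, 0.400 and 0.402 against a true 0.40, so it is not biased.

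**Other settings.**
- A separate simulation with 12 items (df 51) rejected the true model in 60% (symmetric) and 88% (skewed) of samples. With 20 items (df 164) it rejected 98% and 100%. Continuous data gave 6% to 8%. These settings used 60 to 400 replicates.
- With 30 items and 5 symmetric categories, rejection was 100%, but the continuous control also rejected 23%, so part of the excess there is a small-sample effect. No standard-error shortfall was seen (ratio 1.11). This setting had 60 runs.
- At n = 2000 rejection was still 63% (100 runs), so a larger sample does not cure the problem.

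**After the fix.** Unweighted least squares on the same kind of polychoric matrices, with a mean-and-variance-adjusted test:

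T* = n Σ(r − ρ)² × tr(UΓ)/tr[(UΓ)²], on d = [tr(UΓ)]²/tr[(UΓ)²],

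where r and ρ are the observed and fitted correlations, D is the matrix of derivatives of ρ, U = I − D(DᵀD)⁻¹Dᵀ, and Γ is the covariance matrix of the polychorics (times n). Rejection was 5.4% (5 symmetric), 5.9% (5 skewed) and 4.0% (3 categories), with SE/empirical SD of 0.97 to 0.98. Monte Carlo error around 5% is ±1.96 × √(0.05 × 0.95/1000) = ±1.4 points, so all three are compatible with 5%. Γ came from 2000 simulated samples rather than from each data set, so practical performance may be slightly less good.

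**Reuse of one sample, tested separately.** With continuous data, items were selected by exploratory analysis and the resulting structure was refitted on the same sample or on a new sample of 216.

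| Cross-loading SD | T/df, same | T/df, new | CFI, same | CFI, new |
|---|---|---|---|---|
| 0 | 1.04 | 1.04 | 0.988 | 0.987 |
| 0.10 | 1.47 | 1.49 | 0.927 | 0.922 |
| 0.15 | 1.83 | 1.90 | 0.889 | 0.876 |

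Where reuse has an effect, it is small and flatters the fit, which is the opposite direction to the estimator problem.

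**The case against.** The strongest reply is that the article condenses a fuller plan, which might specify scaled statistics. That limits the conclusion to uncorrected maximum likelihood but does not remove it: the article commits to an estimator and names nothing that would repair it.

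It is also fair that no chi-square decision rule or fit cut-off is set, and that nothing says items would be dropped after a rejection. With 5 symmetric categories the average RMSEA (0.043) and CFI (0.967) would not alarm many readers. Harm through item removal is therefore possible, not planned. Exploratory loadings are little affected, so there is no strong case for replacing the estimator there.

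Three stronger readings are tempting, and the document does not support them.
- A reader might infer that standard errors and estimates are seriously wrong. The shortfall at 15 items is modest, none was seen at 30, and the factor-correlation estimate is unbiased.
- A reader might infer that the confirmatory model will be fitted to the people who produced the exploratory structure, and that this too invalidates the fit tests. The article describes one sample and no split, but it does not state the reuse, and the measured effect of reuse is small and in the other direction.
- A reader might say that halves of 216/2 = 108 breach the plan's minimum of 200. That figure is set for the validation phase as a whole. Under the per-item rule, 108/5 = 21.6, so a half would still serve up to 21 items.

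**Conclusion.** The point holds for the confirmatory fit statistics. Maximum likelihood on polychoric correlations, used as stated and without correction, turns a nominal 5% test of a true model into one that rejects about 76% to 99.8% of the time at n = 216 with 15 items. It also shifts mean RMSEA and CFI in the unfavourable direction.

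The exact size depends on the assumed items, categories, skew, loadings and factor correlations, none of which the article gives. The direction was the same in every polychoric setting tried. The conclusion also assumes that no robust correction is applied.

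Reuse of the sample is a separate matter of labelling: a model refitted to the data that suggested it is not independent confirmation, whichever estimator is used.

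**What to change.** - For the confirmatory analysis, keep the polychoric matrix and replace uncorrected maximum likelihood with a least-squares estimator for ordinal items (for example WLSMV, or unweighted least squares). Use a mean-and-variance-adjusted test and robust standard errors. Equivalent robust corrections to maximum likelihood are also acceptable.
- In the exploratory analysis, do not choose the number of factors by the uncorrected maximum likelihood chi-square.
- State which participants the confirmatory model uses, and align the conditional and unconditional statements about it. If it refits the exploratory structure on the same 216, report it as exploratory.

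The cost is a change of estimator in an analysis still in progress and, if the sample is reused, a more modest label. It is best done before the validation results are reported.
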